## Abstract

**Background:**

Cervicogenic dizziness is a disabling condition characterised by postural unsteadiness that is aggravated by cervical spine movements and associated with a painful and/or stiff neck. Two manual therapy treatments (Mulligan’s Sustained Natural Apophyseal Glides (SNAGs) and Maitland’s passive joint mobilisations) are used by physiotherapists to treat this condition but there is little evidence from randomised controlled trials to support their use. The aim of this study is to conduct a randomised controlled trial to compare these two forms of manual therapy (Mulligan glides and Maitland mobilisations) to each other and to a placebo in reducing symptoms of cervicogenic dizziness in the longer term and to conduct an economic evaluation of the interventions.

**Methods:**

Participants with symptoms of dizziness described as imbalance, together with a painful and/or stiff neck will be recruited via media releases, advertisements and mail-outs to medical practitioners in the Hunter region of NSW, Australia. Potential participants will be screened by a physiotherapist and a neurologist to rule out other causes of their dizziness. Once diagnosed with cervciogenic dizziness, 90 participants will be randomly allocated to one of three groups: Maitland mobilisations plus range-of-motion exercises, Mulligan SNAGs plus self-SNAG exercises or placebo. Participants will receive two to six treatments over six weeks. The trial will have unblinded treatment but blinded outcome assessments. Assessments will occur at baseline, post-treatment, six weeks, 12 weeks, six months and 12 months post treatment. The primary outcome will be intensity of dizziness. Other outcome measures will be frequency of dizziness, disability, intensity of cervical pain, cervical range of motion, balance, head repositioning, adverse effects and treatment satisfaction. Economic outcomes will also be collected.

**Discussion:**

This paper describes the methods for a randomised controlled trial to evaluate the effectiveness of two manual therapy techniques in the treatment of people with cervicogenic dizziness for which there is limited established evidence-based treatment.

**Trial registration:**

ACTRN12611000073909

## Background

Dizziness is a very common condition in the community that often leads to physical problems such as unsteadiness and falls, as well as social, emotional and financial issues 
[1]. There are many causes of dizziness, one being a dysfunction in the upper cervical spine 
[1-4]. In this condition, termed cervicogenic dizziness, the non-rotary dizziness is described as imbalance or unsteadiness and is related to movements or positions of the neck. Cervicogenic dizziness is accompanied by a range of symptoms including neck pain, neck stiffness, headache, and less often visual disturbances, nausea, ear fullness, sweating, tinnitus, problems with swallowing, temporomandibular joint pain, upper extremity radiculopathy, general weakness and psychological symptoms such as anxiety and disturbances in concentration and memory 
[5]. Although a disabling condition, there is no established treatment. There is some evidence for manual therapy treatment of this condition but good quality randomised controlled trials (RCTs) are scarce 
[3,6]. The existence of cervicogenic dizziness has been a topic of some controversy 
[7,8] but more recent studies and reports have provided evidence in support of its existence 
[4,9-16].

It has been suggested by Hulse 
[17] that one third of people with cervical dizziness have their onset due to trauma such as whiplash, one third have an insidious onset following spinal degeneration, and one third are due to other causes. Whiplash injuries are experienced by 0.1% of the population 
[18] and the incidence of symptoms of dizziness in whiplash sufferers has been variously reported as 20-58% 
[19], 40-80% 
[20] and as high as 80-90% 
[21-23].

Cervical spondylosis, where the cervical zygapophyseal joints are under abnormal mechanical stress, is a major cause of poor balance and dizziness associated with spinal degeneration 
[19]. This may occur in people with vertebral collapse, decreased cervical disc height or herniated discs, degenerative lesions (e.g. osteoarthritis), inflammatory diseases (e.g. rheumatoid arthritis), vertebral displacement, muscle spasm, or in those wearing cervical collars 
[19,24,25]. The cervical zygapophyseal joints are the most densely innervated of all the spinal joints 
[26] with 50% of all cervical proprioceptors occurring in the joint capsules of C1 to C3 
[17]. In a study by Colledge et al. 
[27] investigating the causes of dizziness in the elderly, the authors attributed dizziness to cervical spondylosis in 65% of cases. In support of this theory, extensive degenerative changes such as osteophytes and discopathy on cervical X-rays have been reported in people with this problem 
[24,28,29]. It is believed that dizziness can also be caused by dysfunction of the deep muscular proprioceptors in the upper cervical spine leading to abnormal input to the vestibular nuclei 
[19]. In a study by Treleaven, Jull and Sterling in 2003, people with whiplash-associated dizziness and/or unsteadiness (n=102) were shown to have significantly greater joint position errors and a higher neck pain index than control subjects (n=44), consistent with cervical mechanoreceptor dysfunction being a likely cause of the symptoms 
[30].

### Manual therapy treatments

In 1991, Brian Mulligan, a New Zealand physiotherapist, introduced a physical therapy treatment for cervicogenic dizziness called Sustained Natural Apophyseal Glides (SNAGs) 
[31]. Although this treatment is used clinically and is accepted in the Physiotherapy profession, there has been very little research to evaluate its efficacy for cervicogenic dizziness. SNAGs have been shown to be an effective treatment for this problem in the short term (12 weeks) 
[4], however no longer term follow-up of this treatment has been undertaken. Geoff Maitland described another form of manual therapy called passive joint mobilisations that are commonly used to treat neck pain, headaches and other neck problems 
[32]. A systematic review of the literature showed there is a lack of quality studies evaluating the treatment of cervicogenic dizziness with manual therapy and no studies evaluating the efficacy of Maitland mobilisations in the treatment of this condition 
[3].

### Study aims

The aim of this paper is to report the study protocol used to investigate the effectiveness of two manual therapy treatments in reducing the symptoms of cervicogenic dizziness and associated pain over 12 months. This will be investigated by comparing the effects of these treatments to each other and to a placebo intervention. Other aims of the study are: 1) to assess the effects of the interventions on cervical range of motion, head repositioning and balance; 2) assess and compare the cost effectiveness of the interventions; and 3) to report any possible adverse effects and treatment satisfaction.

## Methods/Design

A prospective RCT with unblinded treatment and blinded outcome assessment will be conducted in the School of Health Sciences at the University of Newcastle, Australia. Participants (with cervicogenic dizziness) will be randomly allocated to SNAGs, Maitland passive joint mobilisation or placebo groups. Each participant will receive two to six treatments by an experienced physiotherapist over six weeks at the discretion of the treating therapist who will use their clinical judgement to determine the specific dosage based on the participant’s response. Treatment will cease if the participant perceives the condition is adequately improved or if the improvement plateaus, that is, no further improvement is evident over three successive visits.

### Ethics approval

The study design and procedures were approved by the University of Newcastle Human Research Ethics Committee (Protocol Number: H-2009-0377), and the procedures followed were in accordance with the Helsinki Declaration of 1975, as revised in 2000. Written informed consent will be obtained from all participants prior to enrolment in the study.

### Participants and recruitment

Ninety participants with cervicogenic dizziness will be recruited in the Hunter region of NSW, Australia, via media releases and resulting radio interviews and newspaper articles, by advertisements in local newspapers, and by referral from medical practitioners including neurologists (Figure 
1 Flow chart). Inclusion and exclusion criteria are summarised in Table 
1.

**Figure 1 F1:**
[figure not shown]
Flow chart of the research protocol.

**Table 1 T1:** Inclusion and exclusion criteria

**Inclusion criteria:**	
-	has dizziness described as imbalance related to neck movements or positions and a stiff and/or painful neck
-	has had the symptoms present for greater than 3 months
-	18-90 years old

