#### Phone screening

During the phone screening a history will be taken by the physiotherapist to establish that the person does have dizziness described as imbalance or unsteadiness. If the person has any other types of dizziness such as vertigo, migrainous vertigo, pre-syncope, signs and symptoms of vertebral artery ischaemia (dysarthria, drop attacks, facial paraesthesia, syncope), orthostatic hypotension or psychogenic dizziness 
[33] they will be excluded. If the dizziness is described as imbalance or unsteadiness it must be established that the imbalance is not due to another cause including musculoskeletal problems, neuromuscular problems, and conditions affecting the brain such as Parkinson’s disease, stroke, cerebellar ataxia, multiple sclerosis, Vitamin B12 deficiency or alcoholism. Then it must be established that there is a related history of neck pain and or/stiffness. The unsteadiness or poor balance must also be exacerbated by cervical spine movements or positions to be considered to be due to cervicogenic dizziness.

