#### Primary outcome

Severity of dizziness (an average level over the previous week) will be measured with a 100 mm horizontal visual analogue scale (VAS). The VAS has been used successfully to measure dizziness in other studies 
[4,37-39].

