#### Secondary outcomes

1) Frequency of dizziness will be measured on a six-point rating scale (0 = no dizziness, 1 = dizziness less than once per month, 2 = 1–4 episodes of dizziness per month, 3 = 1–4 episodes of dizziness per week, 4 = dizziness once daily, 5 = dizziness more than once a day or constant). This scoring method has been used by several researchers 
[4,8,37,38] to measure frequency of dizziness.

2) Disability caused by dizziness will be measured with the Dizziness Handicap Inventory (DHI). This is a health status measure specifically designed to assess dizziness. The DHI assesses the quality of life using three subscales evaluating the impact of dizziness on the functional, emotional and physical aspects of everyday life 
[40]. The highest possible score is 100, indicating maximum self-perceived handicap. The DHI has been shown to be a highly reliable and responsive tool 
[40-42].

3) Severity of neck pain (an average level over the previous week) will be assessed with a 100 mm VAS. There is much evidence supporting the high validity of the VAS for measuring pain intensity 
[43-47].

4) Global perceived effect will be used to assess satisfaction with treatment and measured by self-assessment on a six-point scale (0 = no benefit, 1 = minimal benefit, 2 = some benefit, 3 = a lot of benefit, 4 = great benefit, 5 = maximal benefit) as used in other studies 
[4,48,49].

5) Posturography will be used to identify and quantify disturbances in balance. Body sway will be measured with a Chattecx Balance Dynamic System (Serial No 1001, Chattecx Corporation, the Chattanooga Group, Tennessee). Recordings will be performed during the following tasks.

· standing erect with the neck in the neutral position with eyes open

· standing erect with the neck in the neutral position with eyes closed

· standing erect with the neck extended

· standing erect with the neck in left rotation

· standing erect with the neck in right rotation

· standing on a moving platform.

Posturography has been used in many studies to assess people with dizziness and has been found to have good correlations with the participant’s symptoms 
[4,6,8,37].

6) A Cervical Range of Motion (CROM) goniometer (Performance Attainment Associates, [name]), which has been shown to be a reliable tool with good validity 

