### Data analysis

#### Sample size calculation

The sample size required is based on an analysis using independent t-tests to test for differences between pairs of treatment groups, with alpha set at 0.05. Three comparisons will be made: the SNAG group compared to the placebo group, the Maitland mobilisation group compared to the placebo group and the SNAG group compared to the Maitland mobilisation group. Sample size calculations were based on a difference between the two groups that would be clinically significant for the main outcome measures, supported by the results of previous research where applicable data existed, and clinical expectations for those factors for which no previous data existed. This was estimated by biostatisticians from the Centre for Clinical Epidemiology and Biostatistics, The University of Newcastle, using other studies with the DHI and VAS as outcome measures 
[41,49,51,52]. The DHI was the primary outcome measure used for sample size calculations, as it is a widely reported measure of self-perceived disability and effect of dizziness on function. It has been shown to have strong validity and short-term test-retest reliability and good internal consistency 
[53,54]. Visual analogue scales have also been used in many studies to measure pain and the main complaint 
[49] and been shown to have high reliability and validity, and a calculation of sample size was also based on VAS data.

Assuming that the standard deviation of DHI scores is 15, then 30 participants per group will give the study 80% power to detect a difference of 11 units between groups for each comparison. Thirty participants per group are also required based on a 0–10 VAS scale (e.g. for dizziness), with a standard deviation of 2.4 and a clinically significant difference of 2 units with a power of 80% and a 5% confidence level.

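### Entry sets no minimum level of dizziness while the primary VAS looks back one week only, so some randomised patients may have little or no room to improve

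*Protocol article*

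**What the plan says.** Table 1 of the protocol article requires that the patient "has dizziness described as imbalance related to neck movements or positions and a stiff and/or painful neck" and "has had the symptoms present for greater than 3 months", and is aged 18 to 90. The three-month rule concerns how long the symptoms have existed, not how strong, frequent or recent they are. The exclusion criteria add no minimum.

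The screening sections follow the same pattern. The phone interview is "to establish that the person does have dizziness described as imbalance or unsteadiness", that is, to establish the type of dizziness. It also asks for a neck history and for aggravation by neck movement or position. The physiotherapist's and neurologist's examinations look for other causes and for signs of neck dysfunction. None of these steps sets a threshold for severity or frequency.

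The Primary outcome section reads: "Severity of dizziness (an average level over the previous week) will be measured with a 100 mm horizontal visual analogue scale (VAS". Among the secondary outcomes is a six-point frequency scale whose lower grades run "0 = no dizziness, 1 = dizziness less than once per month", then 1 to 4 episodes a month (grade 2) and 1 to 4 a week (grade 3). Primary and secondary outcomes are both measured at baseline.

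The Sample size calculation section gives 30 per group for a 0–10 VAS, "with a standard deviation of 2.4 and a clinically significant difference of 2 units with a power of 80% and a 5% confidence level".

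**The concern.** The entry rule and the primary endpoint use different time frames. Entry asks whether the right kind of dizziness has existed for more than three months. The endpoint asks how bad it was in the last seven days. A patient with infrequent episodes can satisfy the first and score near zero on the second. A patient with continuous but very mild dizziness, say 10 mm, is also eligible and can improve by 10 mm at most.

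Randomisation spreads such patients evenly in expectation, so it prevents confounding. It does not prevent dilution: patients with no room to improve pull the mean difference towards zero in both comparisons with placebo and in the comparison of the two manual therapies. At 30 per group, a treatment that works in patients with appreciable dizziness could be missed.

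**Working it through.** **Inputs from the Sample size calculation section.** VAS difference 2 on a 0–10 scale (20 mm on the 100 mm scale), SD 2.4, independent t-test, alpha 0.05 (two-sided assumed, as the article does not say), 30 per group. For the DHI: difference 11, SD 15, 30 per group.

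**Step 1: reproduce the article's figures.**
- DHI: standardised difference 11/15 = 0.733. The t-test needs 30.2 per group for 80% power, and 30 per group gives 79.8%. The stated 30 is reproduced.
- VAS: standardised difference 2/2.4 = 0.833. The t-test needs 23.6, so 24 per group, and 30 per group gives 88.8%. The stated 30 is not reproduced at 80% power. The discrepancy is conservative and leaves slack.

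**Step 2: dilution when low scorers show no effect.** Let f be the share of each arm with no room to improve. The documents do not give f, so every value is an assumption. The expected difference is 2 × (1 − f). With SD held at 2.4 and 30 per group (t-test):

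| f | difference | power |
|---|---|---|
| 0 | 2.0 | 88.8% |
| 10% | 1.8 | 81.5% |
| 20% | 1.6 | 71.9% |
| 30% | 1.4 | 60.3% |
| 40% | 1.2 | 47.8% |

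Power equals 80% at a difference of 1.765, so f = 1 − 1.765/2 = 0.117, or about 12%. The normal approximation gives about 13%.

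**Step 3: partial effect.** If low scorers show half the effect, the difference is 2 × (1 − f/2). At f = 20% this is 1.8 and power is 81.5%. At f = 30% it is 1.7 and power is 77.0%.

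**Step 4: wider SD.** Mixing patients who score 0 with others also changes the spread. Suppose the other placebo patients average μ, the other treated patients average μ − 2, and both have SD 2.4. The variance in an arm is then (1 − f) × 2.4² + f(1 − f) × m², with m = μ or μ − 2, averaged over the two arms. For μ from 4 to 6 (assumed), t-test power is 79% to 71% at f = 10% and 69% to 54% at f = 20%. Holding SD at 2.4 is thus the milder assumption.

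**Step 5: how a blank week can arise.** If episodes fell at random in time (a Poisson process, assumed), the chance of none in 7 days is exp(−rate × 7/30.4). That is 79% at one a month, 63% at two and 40% at four. This illustrates the mechanism only. It does not estimate how many entrants are of this kind.

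**The case against.** The strongest reply is that nothing shows such patients will be common. Dizziness must be related to neck movement or position, must have lasted over three months, and must be troublesome enough for the patient to pass a phone interview and two examinations. Dizziness provoked by movement is not obviously a random event once a month. This stands: f is unknown, and the Poisson figures cannot fill the gap.

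A reader might infer from "1 = dizziness less than once per month, 2 = 1–4 episodes of dizziness per month" that the trial expects to enrol patients with monthly or rarer dizziness. The documents do not support that. It is an outcome scale used at every visit, it also contains a grade for no dizziness, and low grades are needed to record improvement.

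A reader might also infer that low scorers contribute nothing, or that each patient must be able to improve by 2 units. Neither holds. The 2 units is a difference between groups. A patient at 10 mm can still improve by 1 unit on the 0–10 scale, and a patient who scores zero by chance at baseline may have episodes in later weeks that treatment could prevent. The planning values may also come from studies with equally broad entry, so some dilution may already be built in.

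Further, the VAS calculation has slack, the planned mixed model uses repeated visits, and the one-week argument does not touch the DHI. These points reduce the likely loss. The slack is limited, however. The article states no allowance for dropout, and with 27 analysed per group (10% loss, assumed) the tolerable share falls from about 12% to about 7%.

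Finally, Table 1 is introduced as a summary and the full protocol is not shown. But the article spells out the screening test by test, including blood-pressure cut-offs and a 30-second tandem stance, and no minimum level of dizziness appears there either.

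**Conclusion.** The point holds as a possible loss of sensitivity on the primary VAS. Entry sets no minimum level of dizziness, the endpoint covers one week, and patients with little or no dizziness in that week can be randomised. They dilute the between-group difference by an unknown amount.

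If they show no effect, with SD 2.4 and 30 analysed per group, a share of up to about 12% is absorbed, and power is about 72% at 20% and 60% at 30%. A partial effect makes the loss smaller. A wider SD or dropout makes it larger. The documents do not support saying that the trial is underpowered, or that infrequent dizziness will be common among entrants.

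Broad eligibility is a defensible choice and the article does not contradict itself here. The weight lies between an optional suggestion and an advisable change.

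**What to change.** Add one line to Table 1, checked at the baseline assessment before randomisation and using measures already collected:
- dizziness at least weekly on the trial's own frequency scale (grade 3 or higher); and
- a non-trivial baseline VAS, for example at least 20 mm.

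The 20 mm is a pragmatic cut-off. It should not be presented as following from the 2-unit difference, which is a contrast between group means and not an individual threshold. A VAS cut-off alone would admit infrequent cases caught in a bad week, who would tend to score low later in every arm. The frequency condition limits this but does not remove it: under the same random-episode assumption, a patient with one episode a week still has an exp(−1) = 37% chance of a blank week.

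For that reason, include baseline VAS in the primary model, either as a covariate or as a baseline time point with a common mean across arms, so that regression to the mean is handled equally across arms. State that conclusions apply to patients with at least this level of dizziness.

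The cost is a short protocol amendment, somewhat slower recruitment and a narrower population. If few candidates score low, few are turned away, so the cost to recruitment is roughly in proportion to the problem.

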**Exclusion criteria:**	
**Known conditions that would put them at risk of injury:**	
-	inflammatory joint disease
-	spinal cord pathology
-	cervical spine infection
-	bony disease or marked osteoporosis
-	marked cervical spine disc protrusion
-	cervical spine cancer
-	acute nerve root symptoms (severe pain, weakness, pins and needles or numbness in the arm or hand for less than 6 weeks)
-	recent fracture/dislocation of the neck (in the last 3 months)
-	previous surgery to the upper cervical spine
**People will also be excluded if they have the following:**	
-	other types or causes of dizziness, such as vertigo, light headedness, psychogenic dizziness, vertebrobasilar insufficiency
-	other causes of poor balance
-	migraines
-	physiotherapy or similar treatment to the neck in the previous month
-	current pregnancy
-	compensable cases
-	inability to speak or read English

